| Any concurrent chemotherapy, local therapy (except palliative radiotherapy for non-target lesions, eg, radiotherapy, surgery, radiofrequency ablation), biologic therapy, or hormonal therapy for cancer treatment           | Should not be given whilst the patient is on IP treatment (including SoC). (Concurrent use of hormones for non-cancer-related conditions [eg, insulin for diabetes and hormone replacement therapy] is acceptable.)                                                                            |
| Immunosuppressive medications, including, but not limited to, systemic corticosteroids at doses exceeding 10 mg/day of prednisone or its equivalent, methotrexate, azathioprine, and tumor necrosis factor $\alpha$ blockers | Should not be given whilst the patient is on IP treatment (including SoC). (Use of immunosuppressive medications for the management of IP-related AEs or in patients with contrast allergies is acceptable. In addition, use of inhaled, topical, and intranasal corticosteroids is permitted. |
| Live attenuated vaccines                                                                                                                                                                                                     | Should not be given through 30 days after the last dose of IP (including SoC) during the study                                                                                                                                                                                                 |

| Rescue/supportive medication/class of drug:                                                                                                                                                                                             | Usage:                                        |
|------------------------------------------------------------------------------------------------------------------------------------------------------------------------------------------------------------------------------------------------|------------------------------------------------------|
| Concomitant medications or treatments (eg, acetaminophen or diphenhydramine) deemed necessary by the Investigator to provide adequate prophylactic or supportive care, except for those medications identified as “prohibited” as listed above | To be administered as prescribed by the Investigator |

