| 
If toxicity worsens, then treat as Grade 3 or Grade 4.
 
Study drug/study regimen can be resumed once event stabilizes to Grade <math>\leq 1</math> after completion of steroid taper.
                                                                                                                                                                | 
 
– For persistent (<math>>3</math> to 5 days) low-grade (Grade 2) or severe (Grade <math>\geq 3</math>) events, promptly start prednisone 1 to 2 mg/kg/day PO or IV equivalent.
 
                                                                                                                                                                                                                                                                                                                                                                                 |
| 
Patients with endocrinopathies who may require prolonged or continued steroid replacement can be retreated with study drug/study regimen on the following conditions:
                                                                                                                                                                                      | 
 
– Some events with high likelihood for morbidity and/or mortality – e.g., myocarditis, or other similar events even if they are not currently noted in the guidelines – should progress rapidly to high dose IV corticosteroids (methylprednisolone at 2 to 4 mg/kg/day) even if the event is Grade 2, and if clinical suspicion is high and/or there has been clinical confirmation. Consider, as necessary, discussing with the study physician, and promptly pursue specialist consultation.
 
                                                                   |

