| Nephritis or renal dysfunction
(elevated serum creatinine)                                                                                                                                                                                                                                                                                                                                                                                                                                                                                                                                                                                                                                                                                                                                                                                                                                                                                                                                                                                                                                                                                                                                                                                                                                                                          | Any Grade | General Guidance                                                                                                                                                                                                                                                                                        | For Any Grade: 
 
Consult with nephrologist.
 
Monitor for signs and symptoms that may be related to changes in renal function (e.g., routine urinalysis, elevated serum BUN and creatinine, decreased creatinine clearance, electrolyte imbalance, decrease in urine output, or proteinuria).
 
Patients should be thoroughly evaluated to rule out any alternative etiology (e.g., disease progression or infections).
 
Steroids should be considered in the absence of clear alternative etiology even for low-grade events (Grade 2), in order to prevent potential progression to higher grade event.
 
 |

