| 
Grade 1

(serum creatinine > ULN to 1.5 × ULN)
                           | 
No dose modifications.
                                                                                                                                                                                                                                                                                        | 
For Grade 1:
 
 
– Monitor serum creatinine weekly and any accompanying symptoms. 
 
• If creatinine returns to baseline, resume its regular monitoring per study protocol.
 
• If creatinine worsens, depending on the severity, treat as Grade 2, 3, or 4.
 
 
 
– Consider symptomatic treatment, including hydration, electrolyte replacement, and diuretics.
 
– If baseline serum creatinine is elevated above normal, and there is a rise to > 1 to 1.5 × baseline, consider following recommendations in this row.
 
                                                                                                                                                                                                                                                                                                                                                                                                                                                                                    |

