| 
Grade 2

(serum creatinine >1.5 to 3.0 × baseline; >1.5 to 3.0 × ULN)
 | 
Hold study drug/study regimen until resolution to Grade ≤1 or baseline.
 
 
• If toxicity worsens, then treat as Grade 3 or 4.
 
• If toxicity improves to Grade ≤1 or baseline, then resume study drug/study regimen after completion of steroid taper.
 
 | 
For Grade 2:
 
 
– Consider symptomatic treatment, including hydration, electrolyte replacement, and diuretics.
 
– Carefully monitor serum creatinine every 2 to 3 days and as clinically warranted.
 
– Consult nephrologist and consider renal biopsy if clinically indicated.
 
– If event is persistent (>3 to 5 days) or worsens, promptly start prednisone 1 to 2 mg/kg/day PO or IV equivalent.
 
– If event is not responsive within 3 to 5 days or worsens despite prednisone at 1 to 2 mg/kg/day PO or IV equivalent, additional workup should be considered and prompt treatment with IV methylprednisolone at 2 to 4 mg/kg/day started.
 
– Once the patient is improving, gradually taper steroids over ≥28 days and consider prophylactic antibiotics, antifungals, and anti-PJP treatment (refer to current NCCN guidelines for treatment of cancer-related infections).a
 
– When event returns to baseline, resume study drug/study regimen and routine serum creatinine monitoring per study protocol.
 
 |

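### Appendix 1, Grade 2 nephritis: one bullet restarts study drug at return to baseline and omits the completed steroid taper that the adjacent cell requires

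*Protocol*

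**What the plan says.** All the places below are in the Protocol. Most are in Appendix 1, the toxicity management table dated 17 October 2019.

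- **Grade 2 nephritis, Dose Modifications column:** study drug is held, then "If toxicity improves to Grade ≤1 or baseline, then resume study drug/study regimen after completion of steroid taper".
- **Grade 2 nephritis, Toxicity Management column, steroid bullets:** if the event persists beyond 3 to 5 days or worsens, "promptly start prednisone 1 to 2 mg/kg/day PO or IV equivalent". Later, "Once the patient is improving, gradually taper steroids over ≥28 days".
- **Same column, last bullet:** "When event returns to baseline, resume study drug/study regimen and routine serum creatinine monitoring per study protocol".
- **General Considerations regarding Immune-Mediated Reactions, Grade 2:** "Study drug/study regimen can be resumed once event stabilizes to Grade" 1 or lower. The sentence then adds the same completed-taper condition as the Dose Modifications cell.
- **Nephritis, any grade:** "Steroids should be considered in the absence of clear alternative etiology even for low-grade events (Grade 2"), to prevent progression to a higher grade.
- **Nephritis, Grade 1, the parallel bullet:** "If creatinine returns to baseline, resume its regular monitoring per study protocol". It covers monitoring only and says nothing about dosing.
- **Table 2, Prohibited and Rescue Medications:** "Use of immunosuppressive medications for the management of IP-related AEs or in patients with contrast allergies is acceptable". Section 7.2.2 makes the same allowance.

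**The concern.** The last bullet is a positive instruction to restart, with a trigger of its own. It differs from the rule in the neighbouring cell by leaving out the taper. Two investigators with the same patient could each follow a cell of this row and reach opposite decisions, both of them within the Protocol.

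What is at stake is re-exposure to durvalumab, and to tremelimumab while it is being given, in a patient still on steroids for immune-mediated kidney injury. The Dose Modifications cell exists to prevent that. Section 6.2.3 says the three-part combination has never been evaluated and that overlapping toxicity will be hard to assess, so restart rules should be unambiguous.

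**Working it through.** **Step 1. The two triggers side by side**

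| Source | Event status needed | Taper finished? |
|---|---|---|
| Dose Modifications cell, Grade 2 nephritis | Grade ≤1 or baseline | Required |
| General Grade 2 rule | Grade ≤1 | Required |
| Last Toxicity Management bullet, Grade 2 nephritis | Baseline | Not mentioned |

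The appendix does not say which column prevails.

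**Step 2. Can the triggers fall on different days?** Yes. The taper begins at improvement, which comes before or together with return to baseline, and it runs for at least 28 days. Baseline can therefore be reached on any day of the taper.

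**Step 3. Who is affected?** Only patients given steroids. In this row steroids start if the event persists or worsens, and the any-grade guidance says to consider them at Grade 2. Without steroids there is no taper and no conflict on this point.

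**Step 4. Does another rule block a restart during the taper?** The concomitant-medication rules do not, because Section 7.2.2 and Table 2 accept immunosuppressives given for product-related adverse events. Only the Dose Modifications cell and the general Grade 2 rule block it.

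**Step 5. Is the bullet a deliberate exception?** It does not look like one. Where the appendix lets patients restart on continuing steroids (endocrinopathies needing replacement), it says so and sets three conditions: the event is controlled, the patient is clinically stable, and prednisone is no more than 10 mg/day. Nephritis has no such provision. No other Grade 2 immune-mediated row puts a resume instruction in the Toxicity Management column.

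**Step 6. Size of the gap.** The Protocol gives no figure to reproduce. Inputs:

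- Minimum taper: 28 days (Grade 2 nephritis row).
- Durvalumab every 14 days and tremelimumab every 28 days (Section 5.2.1).

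If baseline is reached on taper day d, the bullet allows dosing from day d and the Dose Modifications cell from day 28. The gap is 28 − d days. The number of scheduled durvalumab visits in it is about (28 − d)/14:

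| d | Gap (days) | Gap/14 | Durvalumab doses in the gap |
|---|---|---|---|
| 0 | 28 | 2 | 2 |
| 7 | 21 | 1.5 | 1 or 2 |
| 14 | 14 | 1 | 1 |
| 21 | 7 | 0.5 | 0 or 1 |
| 28 | 0 | 0 | 0 |

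For tremelimumab the maximum is 28/28 = 1 dose. This applies only while tremelimumab is being given: months 1 to 4, or the retreatment period in Section 5.2.2. A taper longer than 28 days widens the gap day for day.

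**The case against.** The strongest reply is that leaving a condition out does not waive it. The bullet follows directly after the taper bullet. Read in order (treat, taper, then resume at baseline), it fits the Dose Modifications cell, and an investigator who waits for both conditions breaks neither instruction. The layout points the same way. Restart is a dosing decision, the Dose Modifications column answers it expressly, and that column is worded more firmly than the Toxicity Management column, which opens as a recommendation. The Grade 2 rows for neuromotor syndromes and myositis also omit the taper at restart, and the general Grade 2 rule is taken to fill that gap. Section 6.2.1 asks for clinical judgment throughout. Finally, the table is a generic guideline with paediatric and hepatocellular carcinoma sections, not text written for this trial.

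Much of this stands. A careful reader will probably reconcile the two cells, and that keeps the point minor. It does not remove the contradiction. No sentence gives one column precedence, and the bullet tells the reader to resume on a stated trigger. The neuromotor and myositis rows differ because they contain no competing restart instruction, so the general rule applies to them without conflict. The generic origin of the text does not change the fact that sites must follow it in this trial.

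**Conclusion.** The concern holds as a minor internal inconsistency that should be corrected. For steroid-treated Grade 2 nephritis, one sentence read literally allows re-dosing during the taper, which the adjacent cell and the general Grade 2 rule do not allow.

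On the minimum taper the difference is at most 28 days, 2 durvalumab doses and 1 tremelimumab dose. That upper end assumes return to baseline on the first day of the taper; the lower end is zero. No taper shape or steroid dose is assumed. Few patients are likely to be affected, though the Protocol gives no incidence from which to count them. No endpoint, sample size or error rate changes.

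The bullet also differs in the other direction. A patient who finishes the taper at Grade 1 but above baseline may restart under the Dose Modifications cell and must wait under the bullet.

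**What to change.** Replace the last Toxicity Management bullet of the Grade 2 nephritis row with wording to this effect: once the event is at Grade ≤1 or baseline and any steroid taper is complete, restart study drug and return to routine creatinine monitoring. This matches the Dose Modifications cell on both the taper and the recovery threshold, and it leaves patients without steroids unaffected.

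Alternatively, limit the bullet to creatinine monitoring, as the Grade 1 row does, and leave restart to the Dose Modifications column.

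Either is a one-sentence edit that can go in with the next amendment. The only cost is that this row would then depart by one sentence from the dated guideline table.

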#### For Grade 3:

Hold study drug/study regimen until resolution to Grade  $\leq 1$  or baseline.

If temporarily holding the study drug/study regimen does not provide improvement of the Grade 3 skin rash to Grade  $\leq 1$  or baseline within 30 days, then permanently discontinue study drug/study regimen.

#### For Grade 4 (or life-threatening):

Permanently discontinue study drug/study regimen.

#### For Grade 3 or 4 (or life-threatening):

- Consult Dermatology.
- Promptly initiate empiric IV methylprednisolone 1 to 4 mg/kg/day or equivalent.
- Consider hospitalization.
- Monitor extent of rash [Rule of Nines].
- Consider skin biopsy (preferably more than 1) as clinically feasible.
- Once the patient is improving, gradually taper steroids over  $\geq 28$  days and consider prophylactic antibiotics, antifungals, and anti-PJP treatment (refer to current NCCN guidelines for treatment of cancer-related infections).a
- Consider, as necessary, discussing with study physician.

| Endocrinopathy                                                                 | Any Grade                                                    | General Guidance | For Any Grade:                                                                                                                                                                                                                                                                                                                                                                  |
|--------------------------------------------------------------------------------|--------------------------------------------------------------|------------------|---------------------------------------------------------------------------------------------------------------------------------------------------------------------------------------------------------------------------------------------------------------------------------------------------------------------------------------------------------------------------------|
| (e.g., hyperthyroidism, thyroiditis, hypothyroidism, Type 1 diabetes mellitus, | (depending on the type of endocrinopathy, refer to NCI CTCAE |                  | 
 
– Consider consulting an endocrinologist for endocrine events.
 
– Consider, as necessary, discussing with study physician.
 
– Monitor patients for signs and symptoms of endocrinopathies. Non-specific symptoms include headache, fatigue, behavior changes, changed mental status, vertigo, abdominal pain,
 
 |

|                                                                                                                                     |                                                                                                                                                                                                                                                                           |                                                                                                                                                                                                                                                                                                                                                                                                                                                                                                                                                                                                                                                                                                                                                                                                                                                                                                                                                                                        |
|-------------------------------------------------------------------------------------------------------------------------------------|---------------------------------------------------------------------------------------------------------------------------------------------------------------------------------------------------------------------------------------------------------------------------|----------------------------------------------------------------------------------------------------------------------------------------------------------------------------------------------------------------------------------------------------------------------------------------------------------------------------------------------------------------------------------------------------------------------------------------------------------------------------------------------------------------------------------------------------------------------------------------------------------------------------------------------------------------------------------------------------------------------------------------------------------------------------------------------------------------------------------------------------------------------------------------------------------------------------------------------------------------------------------------|
| hypophysitis, hypopituitarism, and adrenal insufficiency; exocrine event of amylase/lipase increased also included in this section) | v5.0 for defining the CTC grade/severity)                                                                                                                                                                                                                                 | 
unusual bowel habits, polydipsia, polyuria, hypotension, and weakness.
 
 
Patients should be thoroughly evaluated to rule out any alternative etiology (e.g., disease progression including brain metastases, or infections).
 
Depending on the suspected endocrinopathy, monitor and evaluate thyroid function tests: TSH, free T3 and free T4 and other relevant endocrine and related labs (e.g., blood glucose and ketone levels, HgA1c).
 
For asymptomatic elevations in serum amylase and lipase >ULN and <3×ULN, corticosteroid treatment is not indicated as long as there are no other signs or symptoms of pancreatic inflammation.
 
If a patient experiences an AE that is thought to be possibly of autoimmune nature (e.g., thyroiditis, pancreatitis, hypophysitis, or diabetes insipidus), the investigator should send a blood sample for appropriate autoimmune antibody testing.
 
 |
| Grade 1                                                                                                                      | No dose modifications.                                                                                                                                                                                                                                                    | 
For Grade 1 (including those with asymptomatic TSH elevation):
 
 
Monitor patient with appropriate endocrine function tests.
 
For suspected hypophysitis/hypopituitarism, consider consultation of an endocrinologist to guide assessment of early-morning ACTH, cortisol, TSH and free T4; also consider gonadotropins, sex hormones, and prolactin levels, as well as cosyntropin stimulation test (though it may not be useful in diagnosing early secondary adrenal insufficiency).
 
If TSH < 0.5 × LLN, or TSH > 2 × ULN, or consistently out of range in 2 subsequent measurements, include free T4 at subsequent cycles as clinically indicated and consider consultation of an endocrinologist.
 
                                                                                                                                                                                             |
| Grade 2                                                                                                                      | 
For Grade 2 endocrinopathy other than hypothyroidism and Type 1 diabetes mellitus, hold study drug/study regimen dose until patient is clinically stable.
 
 
If toxicity worsens, then treat as Grade 3 or Grade 4.
 
 | 
For Grade 2 (including those with symptomatic endocrinopathy):
 
 
Consult endocrinologist to guide evaluation of endocrine function and, as indicated by suspected endocrinopathy and as clinically indicated, consider pituitary scan.
 
For all patients with abnormal endocrine work up, except those with isolated hypothyroidism or Type 1 DM, and as guided by an endocrinologist, consider short-term corticosteroids (e.g., 1
 
                                                                                                                                                                                                                                                                                                                                                                                                                                                                              |

|                     |                                                                                                                                                                                                                                                                                                                                                                                                                                                                                                                                                                                                                 |                                                                                                                                                                                                                                                                                                                                                                                                                                                                                                                                                                                                                                                                                                                                                                                                                                                                                                                                                                                                                                                                                                      |
|---------------------|-----------------------------------------------------------------------------------------------------------------------------------------------------------------------------------------------------------------------------------------------------------------------------------------------------------------------------------------------------------------------------------------------------------------------------------------------------------------------------------------------------------------------------------------------------------------------------------------------------------------|------------------------------------------------------------------------------------------------------------------------------------------------------------------------------------------------------------------------------------------------------------------------------------------------------------------------------------------------------------------------------------------------------------------------------------------------------------------------------------------------------------------------------------------------------------------------------------------------------------------------------------------------------------------------------------------------------------------------------------------------------------------------------------------------------------------------------------------------------------------------------------------------------------------------------------------------------------------------------------------------------------------------------------------------------------------------------------------------------|
|                     | 
Study drug/study regimen can be resumed once event stabilizes and after completion of steroid taper.
 
Patients with endocrinopathies who may require prolonged or continued steroid replacement (e.g., adrenal insufficiency) can be retreated with study drug/study regimen on the following conditions:
 
 
1. The event stabilizes and is controlled.
 
2. The patient is clinically stable as per investigator or treating physician's clinical judgement.
 
3. Doses of prednisone are <math>\leq 10</math> mg/day or equivalent.
 
 | 
to 2 mg/kg/day methylprednisolone or IV equivalent) and prompt initiation of treatment with relevant hormone replacement (e.g., hydrocortisone, sex hormones).
 
 
– Isolated hypothyroidism may be treated with replacement therapy, without study drug/study regimen interruption, and without corticosteroids.
 
– Isolated Type 1 diabetes mellitus (DM) may be treated with appropriate diabetic therapy, without study drug/study regimen interruption, and without corticosteroids.
 
– Once patients on steroids are improving, gradually taper immunosuppressive steroids (as appropriate and with guidance of endocrinologist) over <math>\geq 28</math> days and consider prophylactic antibiotics, antifungals, and anti-PJP treatment (refer to current NCCN guidelines for treatment of cancer-related infections).a
 
– For patients with normal endocrine workup (laboratory assessment or MRI scans), repeat laboratory assessments/MRI as clinically indicated.
 
                               |
| Grade 3 or 4 | 
For Grade 3 or 4 endocrinopathy other than hypothyroidism and Type 1 diabetes mellitus, hold study drug/study regimen dose until endocrinopathy symptom(s) are controlled.
 
Study drug/study regimen can be resumed once event stabilizes and after completion of steroid taper.
 
Patients with endocrinopathies who may require prolonged or continued steroid replacement (e.g., adrenal insufficiency) can be retreated with study drug/study regimen on the following conditions:
 
 
1. The event stabilizes and is controlled.
 
           | 
For Grade 3 or 4:
 
 
– Consult endocrinologist to guide evaluation of endocrine function and, as indicated by suspected endocrinopathy and as clinically indicated, consider pituitary scan. Hospitalization recommended.
 
– For all patients with abnormal endocrine work up, except those with isolated hypothyroidism or Type 1 DM, and as guided by an endocrinologist, promptly initiate empiric IV methylprednisolone 1 to 2 mg/kg/day or equivalent, as well as relevant hormone replacement (e.g., hydrocortisone, sex hormones).
 
– For adrenal crisis, severe dehydration, hypotension, or shock, immediately initiate IV corticosteroids with mineralocorticoid activity.
 
– Isolated hypothyroidism may be treated with replacement therapy, without study drug/study regimen interruption, and without corticosteroids.
 
– Isolated Type 1 diabetes mellitus may be treated with appropriate diabetic therapy, without study drug/study regimen interruption, and without corticosteroids.
 
 |

|                                                                                                                                                             |                                                                                                                               |                                                                                                                                                                                                                                                                                                                |                                                                                                                                                                                                                                                                                                                                                                                                                                                                                                                                                                                                                                                   |
|-------------------------------------------------------------------------------------------------------------------------------------------------------------|-------------------------------------------------------------------------------------------------------------------------------|----------------------------------------------------------------------------------------------------------------------------------------------------------------------------------------------------------------------------------------------------------------------------------------------------------------|---------------------------------------------------------------------------------------------------------------------------------------------------------------------------------------------------------------------------------------------------------------------------------------------------------------------------------------------------------------------------------------------------------------------------------------------------------------------------------------------------------------------------------------------------------------------------------------------------------------------------------------------------|
|                                                                                                                                                             |                                                                                                                               | 2. The patient is clinically stable as per investigator or treating physician's clinical judgement.
3. Doses of prednisone are $\leq 10$ mg/day or equivalent.                                                                                                                                              | 
 
Once patients on steroids are improving, gradually taper immunosuppressive steroids (as appropriate and with guidance of endocrinologist) over <math>\geq 28</math> days and consider prophylactic antibiotics, antifungals, and anti-PJP treatment (refer to current NCCN guidelines for treatment of cancer-related infections).a
 
                                                                                                                                                                                                                                                  |
| Neurotoxicity

(to include but not be limited to limbic encephalitis and autonomic neuropathy, excluding Myasthenia Gravis and Guillain-Barre) | Any Grade

(depending on the type of neurotoxicity, refer to NCI CTCAE v5.0 for defining the CTC grade/severity) | General Guidance                                                                                                                                                                                                                                                                                        | For Any Grade: 
 
Patients should be evaluated to rule out any alternative etiology (e.g., disease progression, infections, metabolic syndromes, or medications).
 
Monitor patient for general symptoms (headache, nausea, vertigo, behavior change, or weakness).
 
Consider appropriate diagnostic testing (e.g., electromyogram and nerve conduction investigations).
 
Perform symptomatic treatment with Neurology consult as appropriate.
 

 
                                                                                                             |
|                                                                                                                                                             | Grade 1                                                                                                                | No dose modifications.                                                                                                                                                                                                                                                                                         | For Grade 1: 
 
See "Any Grade" recommendations above.
 
Treat mild signs/symptoms as Grade 1 (e.g. loss of deep tendon reflexes or paresthesia)
 
                                                                                                                                                                                                                                                                                                                                                                                                                                     |
|                                                                                                                                                             | Grade 2                                                                                                                | For acute motor neuropathies or neurotoxicity, hold study drug/study regimen dose until resolution to Grade $\leq 1$ .
For sensory neuropathy/neuropathic pain, consider holding study drug/study regimen dose until resolution to Grade $\leq 1$ .

If toxicity worsens, then treat as Grade 3 or 4. | For Grade 2: 
 
Consider, as necessary, discussing with the study physician. 
 
Obtain Neurology consult.
 
 
 
Sensory neuropathy/neuropathic pain may be managed by appropriate medications (e.g., gabapentin or duloxetine).
 
Promptly start systemic steroids prednisone 1 to 2 mg/kg/day PO or IV equivalent.
 
If no improvement within 3 to 5 days despite 1 to 2 mg/kg/day prednisone PO or IV equivalent, consider additional workup and promptly treat with additional immunosuppressive therapy (e.g., IV IG).
 
 |

